## Abstract

Background: The health of children’s lower extremities and feet is a focus area for caregivers and healthcare professionals such as doctors, school nurses, and podiatrists. Our study aims to investigate the general health status of Danish children’s lower extremities and feet to identify anthropometric parameters that might be preconditions for pain and evaluate for foot diseases and whether they are associated with pain intensity and location, three-dimensional foot dimensions and foot pressure mapping, shoe dimensions, types and intensity of sports activity, quality of life, and foot health. The aim is that we will be able to identify parameters pre-dispositioning for pain, thus providing recommendations for sports activities in relation to the anthropometric conditions of a child as a potential preventive measure for pain. This analysis will be stratified by socioeconomic status on a group level, and this perspective will be able to provide preventative recommendations to prevent pain. Methods: This study is a cross-sectional examination of a thousand children in the first, fifth, and ninth grades in randomized selected Danish primary schools. We will perform a clinical examination of the lower extremities and feet for misalignments, deformities, and diseases as well as rotational status and range of motion. Moreover, we will evaluate their pain levels, sports activities, three-dimensional foot dimensions, plantar pressure, footwear, and patient-related outcome measures (PROMs) for foot health and quality of life. Results: We aim to provide an anthropometrical overview of the lower extremities and feet in children. The obtained basic understanding of healthy normal material in children will be analyzed for its relationships with pain level, sports activities, and socioeconomic status on a group level. This could potentially provide us with an understanding of the factors that impact lower extremity and foot diseases in children. In conclusion, examining children’s lower extremities and feet in Danish primary schools is a step toward identifying areas of improvement in self-care and shoe fitting, mapping podiatry-related needs of care in children’s feet, and providing parental recommendations for preventive actions on shoe fitting and the choice and intensity of sports activity concerning pain. Conclusions: The tenet of this study is a long-term follow-up to evaluate the long-term socioeconomic course on a group level, foot status, and sports activity, using patient-related outcome measures evaluating quality of life and other lifestyle factors such as emotional functioning, social functioning and interaction, and school functioning. Potentially, this will improve children’s quality of life and prevent future diseases.

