
## 1. Introduction

The well-being of children, and the health of children’s feet, is a priority for a range of professionals, such as school nurses, pediatricians, general practitioners, pediatric orthopedics, and podiatrists [1,2]. Social inequality impacts general health in an environment of growing social differences in an increasingly fragmented healthcare system and might raise barriers to accessing qualified health care, thus indicating a need for either rehabilitation and preventive actions or information on healthcare issues concerning children’s diseases of the lower extremities and feet, and a study evaluating the need of healthcare services indicates that this might not reach medical consultation [3,4,5,6,7]. Healthy feet are a prerequisite for many physical activities, and painful feet may inhibit children in physical exercise and give a decreased quality of life [8,9,10]. Children can have painful feet for a plethora of reasons, and structural differences may have an impact on pain and level of activity. Parents and grandparents are concerned that children with in-toeing, flat feet, and curly toes may develop pain or disability, and healthcare workers must be able to differentiate between what are merely physiological variations and what may lead to detrimental conditions as a child grows older. Previous studies indicate that children are born with “flat feet’’ [11,12,13,14] and that the longitudinal medial arch is not fully developed until a child is 6–7 years old [15,16]. Therefore, several studies have failed to show that insoles and special shoes in preschool children change the natural history of flat feet [17]. However, studies examining anthropometric parameters of the lower extremities and feet have not been performed in older children, and little is known about how this affects an older child in relation to pain and how this may affect their participation in sports and other physical activities. Children with flat feet may have a reduced quality of life, thus motivating interventions. A recent study indicates that insoles in older children may change the osseous construction of the foot and thus, may prevent painful flat feet in adults [18]. Therefore, insoles may have the potential to prevent painful flat feet in adults and potentially prevent surgery for this condition in adults [19]. For these motivating reasons, the pediatric orthopedics section of the Rigshospitalet and Hvidovre Hospital, the University of Southern Denmark, and the Association of Danish Podiatrists have started a project for the evaluation and screening of children’s feet and lower extremities in Danish primary schools. Wearing shoes can be underestimated concerning the health of children’s feet, but a too-tight-fitted shoe is known to predispose to hallux valgus and lead to foot pain in children [20,21,22]. Studies in the European setting indicate that children in these countries often wear shoes that are too small [23,24]. The effect of shoe fit also impacts the development of pathological diseases such as apophysitis of the calcanei, and simple ingrown toenails and may give rise to deformities, ingrown toenails, or non-specific foot pain [20,22,25]. In this study, we plan to evaluate this using the commercial technology of 3D surface scanning and evaluate the appropriateness of shoe fitting via the measurement of shoe size. The perspective of this study is that we, in the future, will be able to provide recommendations for preventive actions for children for improvement in the care of the health of children’s lower extremities and feet, thus demonstrating the potential for long-term health and societal financial benefits, such as referral to other health services, guidance on sensible footwear, foot care, and hygiene. The purpose of this project is to identify anthropometric parameters that might be preconditions for pain, evaluate for foot diseases and whether they are associated with pain intensity and location, three-dimensional foot dimensions and foot pressure mapping, shoe dimensions, intensity and type of sports activity, and status of quality of life and foot health according to patient-related outcome measures (PROMs). The aim is that we will be able to identify parameters pre-dispositioning for pain, thus providing recommendations for sports activities in relation to the anthropometric conditions of a child as a potential preventive measure for pain. Our purpose with this study is threefold:To make reference material of the demography of the foot, the rotational status, and the range of motion in joints in the lower extremities of children in Denmark to evaluate if these anthropometric parameters in children influence pain status.Examining the prevalence of pain in children as well as exploring the prevalence of pathologies in children’s feet to evaluate if these conditions in children influence pain status.Evaluating the appropriateness of shoe fitting using commercial 3D technology and foot pressure mapping to evaluate if shoe fitting in children influences foot pain status.

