## 4. Ethical Consideration

### Ethics Approval and Consent to Participate

Before the commencement of the project, we applied to the local ethics committee for ethical approval (H-22002997). The study design was evaluated as a cross-sectional non-intervention study, thus not appropriate for evaluation for approval in accordance with local legal law § 2 or registration as a clinical trial. However, we can confirm that all methods and procedures of this study will adhere to relevant national guidelines and regulations. This includes obtaining informed signed consent from all subjects’ legal guardian(s). If subjects and/or the legal guardians refuse to participate, this will be accepted. Regional registration was obtained in accordance with the Danish Data Protection Agency, as stipulated by Danish law J.nr. 2008-41-2240. 5.3 Ethical Considerations.

The clinical evaluation of children will be a standard orthopedic examination. In our experience, this examination does not cause pain or have side effects/complications, and we expect that the children will not experience pain during the examination, except for minor discomfort. This study entails the evaluation and surface scanning of the children’s legs and feet. All procedures are painless and well-known without known potential side effects or inducing radiation via X-rays. Participants in this study will not experience an increase in the risk of complications or side effects. This study will provide normal materials for orthopedic lower extremity evaluation in children. Previous normal materials for such evaluations are based on a smaller international dataset from decades ago, as described earlier. There is a need to explore this further since the demography has changed during the last decades, and the inclusion of children in this study is justified. We believe that children participating in this study, in addition, will gain information about their anthropologic data as well as their foot and pain statuses. Thus, we believe that the benefits outweigh the risks.

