## 7. Expected Results

The focus on children’s health is essential for children, caregivers, and healthcare professionals such as school nurses, doctors, and podiatrists [1,2]. The lower extremities and feet of typically developed children are an area that causes pain [5]. Specific sports activities seem to impact the health of Danish children’s diseases of the lower extremities and feet, leading to pain [45,46], which, subsequently, will lead to activity restrictions and, if causing musculoskeletal overuse injury, healthcare service needs. To improve the care of children’s feet, a project for the evaluation and screening of children’s feet and lower extremities in Danish primary schools was initiated in the fall of 2022. The interdisciplinary project between physicians, researchers, and podiatrists will examine the extent of lower extremity and foot diseases in children by evaluating children in the first, fifth, and ninth grades of primary school. The project aims to identify areas of improvement in the care of children’s lower extremities and feet with the tenets of creating a prospective database using online submitted PROMs for further follow-up during adolescence and into adulthood and of providing recommendations for preventive actions for healthcare professionals. The study design is a cross-sectional examination of a thousand children, analyzing their clinical status, pain levels, sports activities, foot dimensions and pressures, and footwear. This study will measure foot dimensions using commercial 3D scanning techniques and assess the fitting of footwear. This project will help provide insights into the health of children’s feet and potential mismatches between foot size and footwear that could lead to deteriorating foot health. This project’s findings aim at developing recommendations concerning anthropometric parameters that might be preconditions for pain, the three-dimensional foot dimensions and foot pressure mapping, and the intensity and type of sports activity as a potential preventive measure from the perspective of socioeconomic inequality on a group level and activity status with the tenet of minimizing unintended consequences, such as performing specific high-intensity sports if preconditioned for pain, for Danish children’s foot health. However, as eluded earlier, the need for elucidating these issues is national, but these issues relate to children worldwide, and this project could be expanded internationally since the clinical and instrumental evaluations, commonplace clinical examinations, and PROMs are translated into several languages; thus, this project would be ‘translational across countries’.

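### The aims and promised sports recommendations are worded causally, but a cross-sectional survey with pain assessed at the examination supports only associations with current pain

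*Protocol article*

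**What the plan says.** **Design.** The Abstract states: "This study is a cross-sectional examination of a thousand children in the first, fifth, and ninth grades in randomized selected Danish primary schools". The ethics section agrees: "The study design was evaluated as a cross-sectional non-intervention study". Section 5.3 has pain evaluated when the child is examined, and Section 5.4.2 takes the shoes worn on the examination day. The repeat measurements in Section 6.4 (the pilot and the retest of 50 children) serve reliability.

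**Aims.** The Abstract and Introduction both set out to "identify parameters pre-dispositioning for pain, thus providing recommendations for sports activities in relation to the anthropometric conditions of a child". The first numbered purpose is to build reference material "to evaluate if these anthropometric parameters in children influence pain status". The second (pain and pathology prevalence) and third (shoe fit) close with the same kind of clause. Section 7 ties recommendations to the project's findings and gives as an example of what to minimise "performing specific high-intensity sports if preconditioned for pain".

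**Analysis.** Section 6.3 plans simple bivariate analyses, then multilevel logistic regression by grade for associations between pain and kinematic and alignment variables.

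**Reverse path.** The Introduction says "painful feet may inhibit children in physical exercise and give a decreased quality of life". Section 7 says sport affects children's lower extremities and feet, "leading to pain [45,46], which, subsequently, will lead to activity restrictions".

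**The concern.** Words such as *influence*, *precondition* and *pre-dispositioning* claim that the exposure came before the pain and contributed to it. Nothing described in the article puts exposure before pain: it mentions no date of pain onset and no history of earlier activity. The caveats in Section 7 deal with generalizability, sample size and small subgroups, and are silent on time order.

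The article's own rationale includes a path from pain to reduced activity, so the alternative explanation is not a reviewer's speculation. At stake is the step from finding to advice. If an association arises partly because children in pain have already changed what they do, a recommendation to parents or professionals built on it could be mistaken, and the planned regression would not reveal this.

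**Working it through.** **1. Aims against design.**

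| Element | Where | Supports |
|---|---|---|
| Cross-sectional, non-intervention | Abstract; ethics section; Sections 2.1, 6, 7 | Prevalence, reference values, association |
| Pain assessed at the examination | Section 5.3 | Current pain, not new pain |
| Regression of pain on kinematic and alignment variables | Section 6.3 | Association |
| Predisposing parameters, influence on pain, sports recommendations | Abstract; Introduction; Section 7 | Needs time order and control of confounding |

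The last row goes beyond the other three.

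**2. Which exposures can pain change?** The article states this for activity. It is plausible, though not stated, for footwear, plantar pressure and range of motion. It is unlikely for femoral anteversion, tibial torsion and foot length, where confounding is the main concern.

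**3. Illustration for sport.** The article gives no rates, so every input is an assumption: sport has no effect on pain; 50% of pain-free children practise high-intensity sport; the same share of children with pain did so before; 10% to 30% of those have stopped.

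- Practising among children with pain: 0.50 × (1 − 0.10) = 0.45, or 0.50 × (1 − 0.30) = 0.35.
- Odds among pain-free children: 0.50/0.50 = 1.
- Odds ratio: (0.45/0.55)/1 = 0.82, or (0.35/0.65)/1 = 0.54.

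As counts at the 30% end, with an assumed pain prevalence of 20% in 1000 children: 70 of 200 children with pain practise and 130 do not; 400 of 800 pain-free children practise and 400 do not. Pain is then 70/470 = 14.9% in practisers and 130/530 = 24.5% in the others, with odds ratio (70 × 400)/(130 × 400) = 0.54. A truly protective sport would give the same table.

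**4. Sample size does not help.** At that odds ratio of 0.54, with prevalence 10% to 30% and a two-sided 5% test of two proportions, the chance of a significant result is 37% to 72% in one grade (n = 333) and 82% to 99% at n = 1000. Clustering is ignored, so these are somewhat high.

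**5. The net sign is open.** Section 7 expects some sports to lead to pain, which pushes the odds ratio up. Keep 50% participation among pain-free children and let a share *s* of children with pain have practised before any stopped. The observed odds ratio equals 1 when *s* × (1 − stopped) = 0.50.

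- 10% stopped: *s* = 0.50/0.90 = 0.556; odds ratio before stopping 0.556/0.444 = 1.25.
- 30% stopped: *s* = 0.50/0.70 = 0.714; odds ratio before stopping 0.714/0.286 = 2.5.

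A harmful association of 1.25 to 2.5 would thus be exactly hidden. A larger one would still show as harm, but weakened.

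**The case against.** The best defence is that the design suits the core of each purpose (reference material, prevalence and shoe fit), that the analysis section already says associations, and that the text is hedged with *might* and *potential* and places recommendations in the future. A long-term follow-up is called the tenet of the study. Much of this stands: the fault lies in the causal clauses attached to sound purposes, and a mistaken recommendation is a possibility, not a certainty. But hedging does not remove the plain influence clauses, the Abstract and Introduction derive the recommendations directly from the identified parameters, and no recommendation is made conditional on the follow-up.

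A reader might also infer more than the article supports:

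- **That everything is recorded at one visit.** Sections 5.3 and 6.1 route questionnaires and general information through REDCap, so sport may be recorded at another time. That still does not place it before the pain.
- **That sport will be shown as falsely protective.** The rates above are assumed, and the table is a crude sport-by-pain comparison. The Section 6.3 regression does not name sport as its exposure. The illustrated bias would weaken a warning about high-intensity sport, not create one.
- **That all anthropometric associations may be reversed.** For structural measures this is unlikely.
- **That the study should make no preventive statement at all.** How many shoes miss the 10 mm allowance in Section 5.4.2 can be reported without any association with pain.

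**Conclusion.** The point holds as a mismatch between what the aims claim and what the design can show. Followed as written, the plan would describe cross-sectional associations as predisposing factors and link them to sports recommendations, although the article itself acknowledges a path from pain to activity.

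The conclusion rests on the stated design, the timing of pain assessment and the wording of the aims; it does not depend on the illustration. The odds ratios of 0.82 to 0.54 show only that ordinary rates of stopping could produce a material association with no true effect. Neither the size nor the net sign of any bias in this study can be derived from the article. The matter should be corrected before conclusions are drawn, since Section 6.1 reports that preliminary analysis is under way.

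**What to change.** 1. Keep the three purposes on reference material, prevalence and shoe fit. In the Abstract, Introduction and Section 7, replace the influence, precondition and pre-dispositioning clauses with: *cross-sectional association with current pain*.
2. Add to the Section 7 caveats that exposure and pain are not ordered in time; that reverse causation is possible for sport and plausible for footwear, plantar pressure and range of motion; and that confounding is the main concern for structural measures.
3. State that sports or other pain-prevention recommendations resting on associations with pain will not be drawn from the cross-sectional data alone. They would depend on longitudinal data, if the intended follow-up records pain. Descriptive shoe-fit findings are unaffected.

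The cost is rewording, with no new examination visit and no change in sample size. The downside is a weaker claim from the first report. An analysis of new pain should not be counted as a one-sentence addition: the article describes no follow-up schedule or follow-up pain measure, so unless the full protocol has them, they would need to be planned.

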
## 1. Introduction

The well-being of children, and the health of children’s feet, is a priority for a range of professionals, such as school nurses, pediatricians, general practitioners, pediatric orthopedics, and podiatrists [1,2]. Social inequality impacts general health in an environment of growing social differences in an increasingly fragmented healthcare system and might raise barriers to accessing qualified health care, thus indicating a need for either rehabilitation and preventive actions or information on healthcare issues concerning children’s diseases of the lower extremities and feet, and a study evaluating the need of healthcare services indicates that this might not reach medical consultation [3,4,5,6,7]. Healthy feet are a prerequisite for many physical activities, and painful feet may inhibit children in physical exercise and give a decreased quality of life [8,9,10]. Children can have painful feet for a plethora of reasons, and structural differences may have an impact on pain and level of activity. Parents and grandparents are concerned that children with in-toeing, flat feet, and curly toes may develop pain or disability, and healthcare workers must be able to differentiate between what are merely physiological variations and what may lead to detrimental conditions as a child grows older. Previous studies indicate that children are born with “flat feet’’ [11,12,13,14] and that the longitudinal medial arch is not fully developed until a child is 6–7 years old [15,16]. Therefore, several studies have failed to show that insoles and special shoes in preschool children change the natural history of flat feet [17]. However, studies examining anthropometric parameters of the lower extremities and feet have not been performed in older children, and little is known about how this affects an older child in relation to pain and how this may affect their participation in sports and other physical activities. Children with flat feet may have a reduced quality of life, thus motivating interventions. A recent study indicates that insoles in older children may change the osseous construction of the foot and thus, may prevent painful flat feet in adults [18]. Therefore, insoles may have the potential to prevent painful flat feet in adults and potentially prevent surgery for this condition in adults [19]. For these motivating reasons, the pediatric orthopedics section of the Rigshospitalet and Hvidovre Hospital, the University of Southern Denmark, and the Association of Danish Podiatrists have started a project for the evaluation and screening of children’s feet and lower extremities in Danish primary schools. Wearing shoes can be underestimated concerning the health of children’s feet, but a too-tight-fitted shoe is known to predispose to hallux valgus and lead to foot pain in children [20,21,22]. Studies in the European setting indicate that children in these countries often wear shoes that are too small [23,24]. The effect of shoe fit also impacts the development of pathological diseases such as apophysitis of the calcanei, and simple ingrown toenails and may give rise to deformities, ingrown toenails, or non-specific foot pain [20,22,25]. In this study, we plan to evaluate this using the commercial technology of 3D surface scanning and evaluate the appropriateness of shoe fitting via the measurement of shoe size. The perspective of this study is that we, in the future, will be able to provide recommendations for preventive actions for children for improvement in the care of the health of children’s lower extremities and feet, thus demonstrating the potential for long-term health and societal financial benefits, such as referral to other health services, guidance on sensible footwear, foot care, and hygiene. The purpose of this project is to identify anthropometric parameters that might be preconditions for pain, evaluate for foot diseases and whether they are associated with pain intensity and location, three-dimensional foot dimensions and foot pressure mapping, shoe dimensions, intensity and type of sports activity, and status of quality of life and foot health according to patient-related outcome measures (PROMs). The aim is that we will be able to identify parameters pre-dispositioning for pain, thus providing recommendations for sports activities in relation to the anthropometric conditions of a child as a potential preventive measure for pain. Our purpose with this study is threefold:To make reference material of the demography of the foot, the rotational status, and the range of motion in joints in the lower extremities of children in Denmark to evaluate if these anthropometric parameters in children influence pain status.Examining the prevalence of pain in children as well as exploring the prevalence of pathologies in children’s feet to evaluate if these conditions in children influence pain status.Evaluating the appropriateness of shoe fitting using commercial 3D technology and foot pressure mapping to evaluate if shoe fitting in children influences foot pain status.

This will be examined from the perspective of detecting and clarifying the role of sports activities, pain status, and socio-economic inequalities on a group level in the health of Danish children’s feet.

